## Methods/Design

EFFORT-D is a randomized controlled trial, designed along the Consort-statement guidelines [33], in which outpatients as well as hospitalised depressed patients will be included and randomized in two groups: a control group or an intervention group (*see flow chart in *Figure 1). The control group outpatients receive usual care (i.e. anti-depressive medication and/or cognitive and/or interpersonal therapy). The control group inpatients have their usual treatment program (consisting of pharmacotherapy and/or sociotherapy, psychotherapy, psycho-education and indicated nonverbal therapies) and are allowed to exercise at low intensity as part of their daily program.

**Figure 1 F1:**
[figure not shown]
**Flow chart**.

The intervention group receives 6 months supervised exercise therapy for 1 h a week and is instructed to train unsupervised for 1 h a week during this period (combined about 40 exercise sessions during the intervention period). Both training sessions follow an individualised intervention protocol and are in addition to the usual care program.

Included and randomised patients in the intervention group are invited to take part in Running Therapy (RT). Patients will only be referred to Nordic Walking (NW) in case of clear medical contra-indications against RT, such as muscular-skeleton problems, or if patients have a strong dislike for running which obstructs participation and compliance. The study will run for 27 months, with an 18 months inclusion period during which patients are recruited and randomized. There are four measurements for each patient: at baseline (T0), halfway the 6 month intervention period (T3), at the end of the intervention period (T6), and at follow up, 12 months after baseline (T12). *In *Table 1* the timetable is shown*.

**Table 1 T1:** Events and time table

					Intervention period			Follow-up period
**Procedure**	**Source**	**Person**	**No. of items**	**Duration (min.)**	**T0**	**T3**	**T6**	**T12**

Written informed consent	letter	patient			X			

Demographics^1^	patient file	research assistant			X			

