### Summarized aims and hypothesis of EFFORT-D

The main objective of the study is to assess the effectiveness of exercise therapy (running therapy (RT) or Nordic walking (NW)), in addition to usual care, on depression in adult patients. We hypothesize that adding exercise therapy to usual care will result in a larger reduction in depressive symptoms (as measured with the Hamilton Rating Scale of Depression, (HRSD)) during a 6 month treatment program as well as at 6 months follow-up, compared to usual care without exercise therapy.

Secondary aims are to assess the effectiveness of exercise therapy (RT or NW) on the following outcome measures: 1) Cardiovascular and metabolic risk parameters as fitness (VO2 max, grip strength), BMI, waist circumference, body composition, blood pressure, fasting blood glucose, cholesterol HDL/LDL ratio and CRP, 2) Co-morbid symptoms of anxiety and pain 3) Quality of life, and 4) Cost-effectiveness.

To assess whether there are subgroups of patients who show a larger or less effect of exercise therapy on depression, subgroup analysis will be conducted differentiated on demographic variables (age, sex) and level and type of depression based on the HRSD, personality traits and level of fitness.

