### Procedures and study instruments

Names of eligible patients with their registration number of the electronic patient file (EPD) are provided by the diagnosing psychiatrists to the research assistant, who will make a first check on inclusion and exclusion criteria, informs the participants and asks them to join the study. Written informed consent will be obtained according to prevailing legal requirements before the start of the study. Eligible patients, HDRS ≥ 14 as primary outcome measure, perform the Åstrand submaximal cycling test, physical measures and fill out the questionnaire, after which the participants are randomized. All outcome parameters measured during baseline will be repeated three, six and 12 months after baseline, except for the blood samples (only at T0 and T6). Height is measured according to protocol (Seca 214, Hamburg, Germany) and a bio-impedance scale is used to measure weight and body composition (Omron HBF-510, Omron Healthcare Europe BV, The Netherlands). Waist circumference is measured twice with a tape measure (Seca 201, Hamburg, Germany) at the midpoint between the lower border of the ribs and the upper border of the pelvis. Systolic and diastolic blood pressure are registered twice at rest, using an electronic blood pressure meter (Omron M6 comfort, Omron Healthcare Europe BV, The Netherlands) with an adequate cuff size. Grip-strength is tested according to protocol using a hydraulic hand dynamometer (Jamar J00105, Sammons Preston Rolyan, Bolingbrook, USA). The submaximal Åstrand test [35] will be performed on a stationary bicycle ergometer (Examiner, Lode BV, The Netherlands) and the mean heart rate of the last 2 min of the test will be used to estimate the VO_2_max. Heart rate during this test is registered by a heart rate monitor (Polar RS 800, Electro Oy, Finland).

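### The stated 27-month study duration is three months too short for the 12-month visit that the protocol promises every patient

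*Protocol article*

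**What the plan says.** In the protocol article, the calendar stands in Methods/Design, in the text below Figure 1: "The study will run for 27 months, with an 18 months inclusion period during which patients are recruited and randomized".

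The sentence that follows sets the schedule for each participant. It opens "There are four measurements for each patient: at baseline (T0), halfway the 6 month intervention period (T3" and closes "and at follow up, 12 months after baseline (T12". The section Procedures and study instruments repeats it: "All outcome parameters measured during baseline will be repeated three, six and 12 months after baseline", with an exception for blood samples only. Table 1 marks the HRSD at T12, and it marks the cost questionnaire (TIC-P) and the Euroqol at T0, T6 and T12.

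The T12 visit belongs to the main hypothesis. The aims section expects a larger fall in HRSD "during a 6 month treatment program as well as at 6 months follow-up".

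Nowhere does the article exempt late recruits from T12, set an earlier inclusion cut-off for that visit, or say that follow-up continues after month 27.

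**The concern.** Two adjacent sentences give durations that do not add up. The first fixes the length of the study and of inclusion. The second gives each patient 12 months of follow-up. The stated total is shorter than inclusion plus follow-up.

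What is at stake is the 12-month assessment. It carries the follow-up half of the main HRSD hypothesis. It is also the only time after T6 at which costs and EQ-5D are collected. If visits stopped at month 27, the last recruits would have none of these data at T12, on top of the drop-out that the sample size already allows for. This is not a detail that a fuller protocol or an analysis plan would supply: the article states specific figures, and they conflict.

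**Working it through.** **Inputs from the protocol article**

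- Study duration 27 months, inclusion 18 months, last visit 12 months after baseline (Methods/Design, below Figure 1).
- Difference 2 HRSD points, SD 5, two-sided 5%, power 80%, 100 evaluable and 140 included per group, 30% drop-out (Sample size).

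**Assumption not in the article**

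- Accrual is even over the 18 months, so the last three months bring 3/18 = 16.7% of patients. A range of late shares is shown below.

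**Step 1: the plan's own sample size**

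n per group = 2 × (1.960 + 0.842)² × 5² / 2² = 98.1, rounded up to 99. The article gives 100, which agrees. Inflation for drop-out gives 100 / 0.70 = 143 against the stated 140, which is close. Working back, 140 × 0.70 = 98 evaluable per group. Power at 98 per group is Φ(2 / (5 × √(2/98)) − 1.960) = Φ(2.80 − 1.96) = 80.0%. The fair comparator for any further loss is therefore 98 per group at 80%.

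**Step 2: the calendar**

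- Last T12 visit: 18 + 12 = month 30, three months after month 27.
- Latest inclusion that still allows T12 by month 27: 27 − 12 = month 15.
- Last T6 visit: 18 + 6 = month 24, inside the 27 months. T3 and T6 are complete for everyone.

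This step needs no assumption. Any start-up or close-out time counted within the 27 months would widen the gap.

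**Step 3: size of the loss if month 27 is a hard stop**

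For a late share s, the number without T12 is 280 × s. The number per arm who can reach T12 is 140 × (1 − s), and after drop-out 140 × (1 − s) × 0.70. Power is Φ(2 / (5 × √(2/n)) − 1.960). With s = 3/18:

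- without T12: 280 × 3/18 = 46.7
- able to reach T12: 140 × 15/18 = 116.7 per arm
- after drop-out: 116.7 × 0.70 = 81.7 per arm
- power: Φ(2.556 − 1.960) = 72.4%
- share of all T12 values missing: 1 − (15/18) × 0.70 = 42%, instead of 30%

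| Late share | Without T12 | Evaluable per arm at T12 | Power |
|---|---|---|---|
| 5.6% (1/18) | 15.6 | 92.6 | 78% |
| 11.1% (2/18) | 31.1 | 87.1 | 75% |
| 16.7% (3/18, even accrual) | 46.7 | 81.7 | 72% |
| 25% | 70.0 | 73.5 | 68% |
| 33% | 92.4 | 65.7 | 63% |

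**Step 4: if drop-out does not mean a missing T12 value**

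If everyone who leaves the exercise programme still attends T12, the calendar loss alone leaves 116.7 per arm, and power is about 86%. The figures in Step 3 depend on treating the 30% as missing outcomes.

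**The case against.** The best reply is that the article does not say which sentence governs. If four visits for each patient is the binding commitment, 27 months is simply a misstated duration and no data are lost. That stands. The contradiction is certain, but the loss of data is conditional on month 27 being a hard stop.

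A reader might go further and infer that the T12 part of the hypothesis cannot be tested, or that it would be biased. The article does not support either. Even with a hard stop, about 82 per arm would have T12 data under even accrual. The loss is set by the date of inclusion and not by outcome. Because allocation is balanced within each location (Randomisation, blinding and treatment allocation), it should fall about equally on both arms. The expected cost is precision.

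Three reservations about the 72% also stand:

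- The accrual pattern is not given, hence the range.
- The Sample size section does not name the time point that it powers, so applying 2 points and SD 5 to T12 is a choice.
- Drop-out is not defined there. The Discussion speaks of it in the intervention group, and Compliance and withdrawal keeps people who leave the exercise programme in the intention-to-treat analysis. Some of the 30% may therefore still supply a T12 score.

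None of this removes the mismatch. It limits what can be said about the consequence.

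**Conclusion.** The calendar is wrong as written. Inclusion over 18 months plus a visit at 12 months needs 30 months, and the article states 27. This part is exact and rests on the article's own figures alone.

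The consequence is conditional and confined to T12. Should visits end at month 27, everyone included after month 15 would miss that assessment, while the comparison during treatment would be untouched. Power would be about 72% instead of 80% if four things hold: month 27 is a hard stop, accrual is even, the 2-point difference and SD apply at T12, and the 30% drop-out is missing T12 data in addition to the calendar loss. With other late shares it would lie between about 63% and 78%. Confidence is high for the mismatch and moderate at most for the size of the effect on power.

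**What to change.** Restate the study duration as at least 30 months from first inclusion, so that every patient's T12 visit is collected. The cost is three more months of follow-up visits that the schedule already promises. The correction should be settled before month 27, because a T12 visit that is not made cannot be recovered.

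If month 27 is fixed, say explicitly that patients included after month 15 have no T12 visit, and restate the sample size and power for T12 accordingly. The cost is lower precision at T12, of the order shown above.

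Closing inclusion at month 15 would also make the calendar fit, but it is not a cheap alternative. Under even accrual it leaves 280 × 15/18 = about 233 patients, which reduces numbers at T3 and T6 too. Keeping 280 would need 18/15 = 1.2 times the planned rate, that is 20% faster recruitment, and the Discussion already allows that the target may not be reached in time.

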**Depression**								

Depression history^2^	patient file	research assistant	2		X			

HRSD^3^	interview	blind rater	17	20	X	X	X	X

IDS-SR^4^	questionnaire	patient	30	10	X	X	X	X

Bearableness (VAS)	questionnaire	patient	1		X	X	X	X

**Metabolic syndrome**								

Length	physical test	research assistant		1	X			

Weight	physical test	research assistant		1	X	X	X	X

Waist circumference	physical test	research assistant		1	X	X	X	X

Blood pressure	physical test	research assistant		1	X	X	X	X

Smoking/alchohol intake	questionnaire	patient		1	X	X	X	X

Laboratory assesment^6^	physical test	laboratory		2	X	X	X	X

**Quality of Life**								

WHO-DAS^7^	questionnaire	patient	36		X	X	X	X

**Pain**								

GCPS^8^	questionnaire	patient	7		X	X	X	X

Bearableness (VAS)	questionnaire	patient	1		X	X	X	X

**Anxiety**								

BAI^9^	questionnaire	patient	21		X	X	X	X

**Cost effectiveness**								

TIC-P^10^	quest./pnt file	pnt/research assistant		26	X		X	X

Euroqol	questionnaire	patient		5	X		X	X

Subjective health (VAS)	questionnaire	patient		1	X		X	X

**Fitness**								

Submaximal cycle test	physical test	research assistant		10	X	X	X	X

Grip strength	physical test	research assistant		2	X	X	X	X

Exercise intensity (HR)^11^	physical test	exercise instructor			during training sessions			

**Personality**								

NEO PI-R^12^	questionnaire	patient	60		X			

**Physical activity**								

SQUASH^13^	questionnaire	patient	12		X	X	X	X

**Additional Measures**								

LEQ^14^	questionnaire	patient	12		X	X	X	X

Compliance	registration	exercise instructor			during training sessions			

POMS^15^	questionnaire	patient	32		during training sessions			

Evaluation Intervention^16^	questionnaire	patient					X	

1: Date of birth, sex, education, ethnicity, income, professional status, living situation, marital status

2: Number and duration of former episodes, duration current episode

3: Hamilton Rating Scale of Depression (or HAMD)

4: Inventory of Depressive Symptomatology - Self Report

6: fasting glucose, triglycerides, total cholesterol, HDL- cholesterol, cholesterol/HDL-ratio, creatinine, MDRD

7: World Health Organisation- Disability Assessment Schedule

8: Graded Chronic Pain Scale

9: Beck Anxiety Inventory

10: Trimbos/iMTA questionnaire for Costs associated with Psychiatric Illness

11: Polar RS 800 CX Run

12: Revised NEO Personality Inventory

13: Short QUestionnaire to ASses Health enhancing physical activity

14: Life Events Questionnaire

15: Profile of Mood State

16: Only for patients who participated in the intervention

### Study population

The study population consists of adult patients diagnosed by a clinician with a depression or bipolar disorder with depressive mood, who are or will be treated in GGZ Centraal Mental Hospitals or Symfora-Meander Hospital. Patients aged between 18-65, with a DSM-IV diagnoses of unipolar, bipolar depression or seasonal depression not responding to light therapy (10 sessions of 1 h), a baseline Hamilton Rating Scale of Depression (HRSD) score ≥14 and (will be) treated for depression, are included.

Criteria for exclusion are: a depression as part of a psychotic disorder, schizophrenia, schizoaffective disorder or obsessive compulsive disorder, anxiety disorder as primary diagnosis, patients in long stay facilities (including day-care) or with complex pathology and treatment resistant depression (inpatients, treated by protocol more than 6 months with no remission); patients with significant cardiovascular disease or other medical conditions as contra-indication for exercise therapy, walking and/or running such as joint and hip pathology; alcohol/drugs dependence as a primary diagnosis, pregnancy, high suicide risk with treatment on a closed ward, or already being physically active on a regular basis (2-3 times a week on a high-intensity).

### Sample size

Following earlier RCTs [34] it is expected that patients in the usual care group (controls) will respond with a mean reduction in HRSD of six points. Adding exercise to usual care is expected to result in a decline of at least eight points in HRSD score (thus two extra points). To detect this difference, with an α (two-tailed) of 5% and a power (1-β) of 80%, using two equal groups and a standard deviation of 5 points, 100 patients are needed in each group. Taking 30% drop-out into account, 140 patients have to be included in each group.

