### Compliance and withdrawal

In order to improve compliance during the intervention period, a protocol will be followed concerning missed exercise therapy sessions by participants. This protocol includes: 1) active approach by the exercise instructor in case of no show, and 2) encouragement of other participants to contact each other in case of no show. Participants can withdraw at any time for any reason without any consequences. Also, the investigator can decide to withdraw a participant from the study for urgent medical reasons. Participants who withdraw from the intervention will be asked the reason(s) for drop-out but will be retained in the study for the intention to treat analysis.

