### Statistical analyses

Comparability of the intervention and control groups will be examined for the baseline measurements. If necessary, analyses will be adjusted for baseline differences. The primary analysis of the data set will be according to the 'intention to treat' principle. A secondary 'per protocol' analysis will be done taking into account the level of compliance and the amount of exercise during the intervention period. Usual daily physical activity, tobacco smoking and alcohol intake will be treated as confounders.

Differences in remission rates (and other categorical outcomes) between the experimental groups are examined by contingency table Chi-square statistics. Differences in mean scores on continuous outcomes (e.g. HRSD) between the intervention groups are examined by analysis-of-variance.

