## Discussion

The aim of this study is to investigate the effectiveness of aerobic exercise therapy (RT or NW) on depression in adult patients in addition to usual care. Also, the effect of physical exercise on frequently existing co-morbid diseases or risk factors for such disorders as metabolic syndrome is an objective of this study.

This is the first well conducted add-on randomised controlled high-quality trial into the effect of aerobic exercise on depression with a correct randomisation procedure, blinded outcome assessment, intention to treat analysis, study into cost-effectiveness, quality of life and long-term follow-up as was advised in earlier publications. EFFORT-D can therefore contribute to stronger evidence for this type of intervention, which can result in more specified recommendations for clinical practice. Another strength of this study is the fact that also severely clinically depressed patients, who are mostly excluded in other studies, will be included. A relatively greater effect of exercise in this subgroup of severely depressed patients is possible. A challenge of the study lies in the motivational techniques needed to exercise with depressed patients, which is proven to be difficult [52] and it will take a serious effort not to exceed the calculated 30% drop-out patients in the intervention group. Because this study is supported by a strong hypothesis and minimal negative side effects are expected, one-tailed statistical analysis is also possible if the large number of included participants can't be reached within the planned time. Furthermore, the diversity of outcome measures makes it possible to distinguish more explicitly those depressed patients that could benefit most from exercise.

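### The 30% allowance removes drop-outs from the power calculation, but the primary intention-to-treat analysis keeps patients who leave the exercise programme, so the stated 80% power is conditional

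*Protocol article*

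**What the plan says.** The Sample size section expects that usual-care patients "will respond with a mean reduction in HRSD of six points" and that adding exercise brings "a decline of at least eight points in HRSD score (thus two extra points". It concludes, "using two equal groups and a standard deviation of 5 points, 100 patients are needed in each group", at two-sided 5% and 80% power. The allowance follows: "Taking 30% drop-out into account, 140 patients have to be included in each group". Drop-out is not defined there.

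Three other sections bear on what it means:

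- **Compliance and withdrawal:** participants who leave the intervention "will be asked the reason(s) for drop-out but will be retained in the study for the intention to treat analysis".
- **Statistical analyses:** "The primary analysis of the data set will be according to the 'intention to treat' principle". Continuous outcomes such as the HRSD are compared by analysis of variance. No rule for missing scores is given.
- **Discussion:** straight after the difficulty of motivating depressed patients to exercise, the article says it will be hard "not to exceed the calculated 30% drop-out patients in the intervention group". The only calculation this can point back to is the one in Sample size.

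**The concern.** Losing a patient's outcome and losing a patient's exercise have different consequences. Missing outcomes reduce the number analysed, and recruiting more patients by the factor 1/(1 − d) restores it. A patient who stops exercising but is still rated stays in the number analysed and may pull the exercise-arm mean towards control. That shrinks the difference, and the 1/(1 − d) allowance is not built for it.

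The protocol uses a single 30% figure. Sample size treats it as the first kind of loss, the Discussion ties it to the intervention arm, and the withdrawal and analysis sections keep those who leave the intervention in the primary analysis. If the 30% is largely withdrawal from exercise, the published power does not describe the primary contrast. Separately, if patients who stop exercising also miss the HRSD, a plain ANOVA with no further rule would leave them out, with a risk of attrition bias.

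**Working it through.** **Inputs.** From Sample size: difference 2 points (8 − 6), SD 5, two-sided α 0.05, power 80%, equal groups, 100 and then 140 per group, drop-out 30%. Assumed, because the protocol gives no figure: the share *b* of the 2-point benefit kept by patients who stop exercising.

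**Step 1: reproduce 100.** n = 2 × (1.96 + 0.84)² × 5² / 2² ≈ 98 per group; the exact t-test needs 99.1, so 100. The stated figure is confirmed. Power at 100 per group is 80.4%.

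**Step 2: reproduce 140.** 100 / (1 − 0.30) = 142.9, so 143; the stated 140 is within 3% of this. The alternative, 100 × 1.30 = 130, does not match. So 140 comes from treating about 30% as contributing no outcome: 140 × 0.70 = 98 per group. The standard error is 5 × √(2/98) = 0.714, and t-test power at 2 points is 79.6%.

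**Step 3: keep everyone, with 30% of the exercise arm stopping.** Difference = 2 × (0.70 + 0.30 × *b*). Standard error = 5 × √(2/140) = 0.598. Two-sided t-test:

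| Share of benefit kept, *b* | Difference | Power, 140 per group | n per group for 80% |
|---|---|---|---|
| 0 | 1.40 | 64.6% | 202 |
| 0.25 | 1.55 | 73.4% | 165 |
| 0.50 | 1.70 | 80.9% | 137 |
| 0.75 | 1.85 | 87.0% | 116 |
| 1 (2 points is already the intention-to-treat effect) | 2.00 | 91.5% | 100 |

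A normal approximation gives 64.9%, 73.7%, 81.2%, 87.2% and 91.7%. Letting the SD grow because the exercise arm becomes a mixture (√(25 + 0.3 × 0.7 × 2²) = 5.08 at *b* = 0) costs less than one further percentage point.

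**Step 4: break-even.** With 140 per group, 80% power needs a difference of 1.68 points. Solving 2 × (0.70 + 0.30 × *b*) = 1.68 gives *b* = (0.84 − 0.70) / 0.30 = 0.47.

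**Step 5: a mixture of both kinds of loss.** Suppose a share *L* of each arm has no outcome, and the rest of the exercise arm's 30% is measured with no added benefit. Then the difference is 2 × 0.70 / (1 − *L*) and n = 140 × (1 − *L*). At *L* = 0.10: 1.56 points, n = 126, power 69%. At *L* = 0.20: 1.75 points, n = 112, power 74%. At *L* = 0.30 this returns to Step 2.

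**The case against.** The strongest reply is that nothing is wrong. The 30% is applied to both groups, and controls have no exercise programme to leave, so it can be read as missing outcomes. Dividing by (1 − d) is then the usual allowance and is compatible with intention to treat. The Discussion may mean only that staying within 30% will be hardest in the exercise arm. The 2 points is described as what adding exercise to usual care achieves, as a minimum, and is not restricted to patients who complete the programme. If it is already the intention-to-treat effect and everyone is measured, power is about 92%. Even with dilution, 140 per group still gives about 81% when half the benefit is kept.

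Much of this stands. The arithmetic is sound, and the passages can be reconciled on one reading. But the protocol does not say which reading it intends. Besides the Discussion, the section on additional measures in the intervention group and the section on compliance both use dropping out for leaving the therapy, so withdrawal from exercise is a natural reading.

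A reader might go further and infer that the 80% belongs to a completer analysis, that the ANOVA uses observed scores at one visit only, that losses fall mostly in the exercise arm, or that the result is biased in favour of exercise. The documents support none of these. The analysis section names analysis of variance without limiting it to observed scores or to one visit. Handling of missing scores may sit in a fuller document that is not shown. No rate or direction of missing HRSD is given by arm.

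**Conclusion.** The point holds as an unresolved tension, not as an arithmetic error. The 80% applies to about 98 to 100 analysed patients per group with an undiluted 2-point difference. The sample size makes no allowance for dilution by patients who stop exercising and stay in the primary analysis.

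If the 30% is withdrawal from exercise and all are measured, power lies between about 65% and 92%, depending on the share of benefit kept. It drops below 80% only when that share is under about half. The range rests on the protocol's own difference and SD, on 30% of the exercise arm stopping, and on an assumed share kept.

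Attrition bias is a risk only if patients who stop exercising also miss the HRSD. It is not a demonstrated fault.

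**What to change.** 1. **Analysis.** Replace the stated ANOVA with a likelihood-based mixed model of HRSD at T3, T6 and T12. Use all available scores from every randomised patient, adjust for baseline HRSD and location (randomisation is done separately at each location), and add a sensitivity analysis for departures from missing at random. Table 1 already schedules the HRSD at all these visits.
2. **Power statement.** Keep 140 per group. State whether the 30% is withdrawal from exercise or missing HRSD, and whether 2 points is the intention-to-treat difference. Present the 80% as conditional on those answers, with the range of about 65%, 73%, 81% and 92% for none, a quarter, half and all of the benefit kept, labelled as assumptions.

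The cost is a little more analysis work and a possibly less favourable power statement. No extra patients or visits are needed.
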